### Site Burden

| Site Burden                                                                                                             |                                                                                                                                                                                       |                                                          |               |
|-------------------------------------------------------------------------------------------------------------------------|---------------------------------------------------------------------------------------------------------------------------------------------------------------------------------------|----------------------------------------------------------|---------------|
| 
After training questionnaire
 [figure not shown] | 
How do you think the new devices can be compared to the reference EEG system in each of the following steps?
 
1: worse
2: identical
3: better
4: much better
 |                                                          |               |
|                                                                                                                         | Set-up time participant preparation time                                                                                                                                              | Participant's comfort and acceptability during recording | Clean-up time |
|                                                                                                                         | Device #1                                                                                                                                                                             |                                                          |               |
|                                                                                                                         | Device #2                                                                                                                                                                             |                                                          |               |
|                                                                                                                         | Device #3                                                                                                                                                                             |                                                          |               |
| 
Please rank the devices in order of preferences.
                                                                 |                                                                                                                                                                                       |                                                          |               |

|                                    | 
 
 Device #1
 
 Device #2
 
 Device #3
 
 Standard EEG Device
 
 
 
● Why did you choose your preferred device as the best one?
 
● Why did you choose your less preferred device as the worst?
 
● How many years of experience in running EEG experiments do you have? 
 
 No previous experience
 
 1 to 5 years
 
 5 to 10 years
 
 More than 10 years
 
 
 
● How many years of experience in running clinical trials do you have? 
 
 No previous experience
 
 1 to 5 years
 
 5 to 10 years
 
 More than 10 years
 
 
 
● Do you have a previous experience with the Standard EEG device? 
 
 YES
 
 NO
 
 
 
● Do you have a previous experience with new wireless EEG device? 
 
 YES
 
 NO
 
 
 
● Anything to add? (Free comments)
 
 |                                               |                                                |                                               |                  |           |  |  |  |           |  |  |  |           |  |  |  |
|------------------------------------|---------------------------------------------------------------------------------------------------------------------------------------------------------------------------------------------------------------------------------------------------------------------------------------------------------------------------------------------------------------------------------------------------------------------------------------------------------------------------------------------------------------------------------------------------------------------------------------------------------------------------------------------------------------------------------------------------------------------------------------------------------------------------------------------------------------------------------------------------------------------------------------------------------------------------------------------------------------------------------------------------------------------------------------------------------------------------------------------------------------------------------------------------------------------------------------------------------------------------------------------------------------------------------------------------------------------------------------------------------------------------------------------------------------------------------------------------------------------------------------------------|-----------------------------------------------|------------------------------------------------|-----------------------------------------------|------------------|-----------|--|--|--|-----------|--|--|--|-----------|--|--|--|
| After DR (dummy run) questionnaire | 
How do you think the new devices can be compared to the reference EEG system in each of the following steps?
 
1: worse
2: identical
3: better
4: much better
 
  
 	Set-up time
participant
preparation time	Participant's
comfort
acceptability and	Clean-up
time	
   
 Device #1				
 
 Device #2				
 
 Device #3				
  
 
 
● Please rank the devices in order of preferences. 
 
 Device #1
 
 Device #2
 
 Device #3
 
 Standard EEG Device
 
 
 
                                                                                                                                                                                                                                                                                                                                                                                                                                                                                                                            |                                               | Set-up time
participant
preparation time | Participant's
comfort
acceptability and | Clean-up
time | Device #1 |  |  |  | Device #2 |  |  |  | Device #3 |  |  |  |
|                                    | Set-up time
participant
preparation time                                                                                                                                                                                                                                                                                                                                                                                                                                                                                                                                                                                                                                                                                                                                                                                                                                                                                                                                                                                                                                                                                                                                                                                                                                                                                                                                                                                                                                                    | Participant's
comfort
acceptability and | Clean-up
time                               |                                               |                  |           |  |  |  |           |  |  |  |           |  |  |  |
| Device #1                          |                                                                                                                                                                                                                                                                                                                                                                                                                                                                                                                                                                                                                                                                                                                                                                                                                                                                                                                                                                                                                                                                                                                                                                                                                                                                                                                                                                                                                                                                                                   |                                               |                                                |                                               |                  |           |  |  |  |           |  |  |  |           |  |  |  |
| Device #2                          |                                                                                                                                                                                                                                                                                                                                                                                                                                                                                                                                                                                                                                                                                                                                                                                                                                                                                                                                                                                                                                                                                                                                                                                                                                                                                                                                                                                                                                                                                                   |                                               |                                                |                                               |                  |           |  |  |  |           |  |  |  |           |  |  |  |
| Device #3                          |                                                                                                                                                                                                                                                                                                                                                                                                                                                                                                                                                                                                                                                                                                                                                                                                                                                                                                                                                                                                                                                                                                                                                                                                                                                                                                                                                                                                                                                                                                   |                                               |                                                |                                               |                  |           |  |  |  |           |  |  |  |           |  |  |  |

|                                                                                                                                       |                                                                                                                                                                                                                                                                                                                                                                                                                                                                                                                                                                                                                                            |
|---------------------------------------------------------------------------------------------------------------------------------------|--------------------------------------------------------------------------------------------------------------------------------------------------------------------------------------------------------------------------------------------------------------------------------------------------------------------------------------------------------------------------------------------------------------------------------------------------------------------------------------------------------------------------------------------------------------------------------------------------------------------------------------------|
|                                                                                                                                       | 
 
• Why did you choose your preferred device as the best one?
 
• Why did you choose your less preferred device as the worst?
 
• Anything to add? (free comments)
 
                                                                                                                                                                                                                                                                                                                                                                                                           |
| Exit debrief for the experimental day questionnaire [figure not shown] | 
Rules (on screen) = Please answer to the next 4 questions, your answers will be used to define your preference list of the systems
 
 
• Please rank the devices in order of preferences.             
 
○ Device #1
 
○ Device #2
 
○ Device #3
 
○ Standard EEG Device
 
 
 
• Why did you choose your preferred device as the best one?
 
• Why did you choose your less preferred device as the worst?
 
• Anything to add? Please explain if you have changed your ranking (free comments)
 
 |

|                                                                                                                                                            |                                                                                                                                                                                                                                                                                                                                                                                                                                                                                                                                                                                                                                                                               |
|------------------------------------------------------------------------------------------------------------------------------------------------------------|-------------------------------------------------------------------------------------------------------------------------------------------------------------------------------------------------------------------------------------------------------------------------------------------------------------------------------------------------------------------------------------------------------------------------------------------------------------------------------------------------------------------------------------------------------------------------------------------------------------------------------------------------------------------------------|
| Interim debrief clean-up (to place after each session with one system) [figure not shown] | 
 
• Did the participant have problematic hair?             
 
○ YES
 
○ NO
 
○ Why? (free comment)
 
 
 
                                                                                                                                                                                                                                                                                                                                                                                                                                                              |
| VAS Set-up                                                                                                                                                 | 
How easy was it to set-up the device?
 
Very difficult  ← →  Very easy
 
 
• How long does it take to set-up the device? (answer expected in minutes)
 
• Do you think that the comfort of the participant was negatively impacted by the device?             
 
○ YES
 
○ NO
 
○ No opinion
 
 
 
 |
| VAS Clean-up                                                                                                                                               | 
How easy was it to clean-up the device?
 
Very difficult  ← →  Very easy
 
 
• How long does it take to clean-up the device? (answer expected in minutes)
 
                                                                                                                                                                                                         |

|  |                                  |
|--|----------------------------------|
|  | Anything to add? (free comments) |
|--|----------------------------------|

| Exit of the study | 
Rules (on screen) = Please answer to the next 4 questions, your answers will be used to define your preference list of the systems
 
 
● Please rank the devices in order of preferences.
 
○ Device #1
 
○ Device #2
 
○ Device #3
 
○ Standard EEG Device
 
● Why did you choose your preferred device as the best one?
 
● Why did you choose your less preferred device as the worst?
 
 
From 1 (worse) to 4 (definitely better), rate the following points in comparison with the standard EEG device
 
  
 	Set-up time
participant preparation
time	Participant's comfort
and acceptability	Clean-up
time	
   
 Device #1				
 
 Device #2				
 
 Device #3				
  
 
 
● Anything to add? Please explain if you have changed your ranking (free comments)
 
 |                                            | Set-up time
participant preparation
time | Participant's comfort
and acceptability | Clean-up
time | Device #1 |  |  |  | Device #2 |  |  |  | Device #3 |  |  |  |
|-------------------|------------------------------------------------------------------------------------------------------------------------------------------------------------------------------------------------------------------------------------------------------------------------------------------------------------------------------------------------------------------------------------------------------------------------------------------------------------------------------------------------------------------------------------------------------------------------------------------------------------------------------------------------------------------------------------------------------------------------------------------------------------------------------------------------------------------------------------------------------------------------------------------------------------------------------------------------------------------------------------------------------------------------------------------------------------------------------------------------------------------------------------------------------------------------------------------|--------------------------------------------|------------------------------------------------|--------------------------------------------|------------------|-----------|--|--|--|-----------|--|--|--|-----------|--|--|--|
|                   | Set-up time
participant preparation
time                                                                                                                                                                                                                                                                                                                                                                                                                                                                                                                                                                                                                                                                                                                                                                                                                                                                                                                                                                                                                                                                                                                                           | Participant's comfort
and acceptability | Clean-up
time                               |                                            |                  |           |  |  |  |           |  |  |  |           |  |  |  |
| Device #1         |                                                                                                                                                                                                                                                                                                                                                                                                                                                                                                                                                                                                                                                                                                                                                                                                                                                                                                                                                                                                                                                                                                                                                                                          |                                            |                                                |                                            |                  |           |  |  |  |           |  |  |  |           |  |  |  |
| Device #2         |                                                                                                                                                                                                                                                                                                                                                                                                                                                                                                                                                                                                                                                                                                                                                                                                                                                                                                                                                                                                                                                                                                                                                                                          |                                            |                                                |                                            |                  |           |  |  |  |           |  |  |  |           |  |  |  |
| Device #3         |                                                                                                                                                                                                                                                                                                                                                                                                                                                                                                                                                                                                                                                                                                                                                                                                                                                                                                                                                                                                                                                                                                                                                                                          |                                            |                                                |                                            |                  |           |  |  |  |           |  |  |  |           |  |  |  |

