| Secondary | To compare the participant burden between three new EEG systems and a standard clinical EEG system                                      | 
 
- Subjective comfort assessed at multiple time points during a recording session
 
- Interim debrief obtained after recording with each device for detailed feedback on each device
 
- Exit debrief at the end of a recording day including a subjective rank ordering of devices from best to worst
 
- Exit debrief at the end of the study including a subjective rank ordering of devices for the best and the worse one as well as some explanation of the selection
 
 |
| Secondary | To compare the site (Technician) burden between three new EEG systems and a standard clinical EEG system                                | 
 
- Set-up (from installation of the system to start of the recording) and clean-up timings for each EEG device
 
- Interim debriefs on ease of clean up
 
- Exit debrief at the end of a recording day including a subjective rank ordering of devices for the best and the worse one
 
- Exit debrief at the end of the study including a subjective rank ordering of devices for the best and the worse one as well as some explanation of the selection
 
                  |

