### **Statistical analysis**

For all quantitative questionnaires (VAS) as well as the timing data, univariate statistics and linear modelling to assess differences in ratings between the test devices and the gold-standard clinical wet system will be performed.

Summary overviews of overall preferred rank orders and answers to specific questions will be constructed.

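### The 1–4 staff grid comparing each new device with the reference can grade degrees of better but not of worse, and its end-of-study form does not say where 'identical' sits

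*Protocol*

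**What the plan says.** Section 10.5.1 of the protocol places all questionnaires in Appendix 3, so the response options are fixed there.

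- **After training and after the dummy run (Appendix 3, Site Burden).** Both forms ask "How do you think the new devices can be compared to the reference EEG system in each of the following steps", with a grid of three new devices by three topics: set-up and preparation time, participant comfort and acceptability, and clean-up time. Both give the codes "1: worse 2: identical 3: better 4: much better".
- **Exit of the study (Appendix 3, Site Burden).** The grid has the same devices and topics. The instruction is "From 1 (worse) to 4 (definitely better), rate the following points in comparison with the standard EEG device", and codes 2 and 3 carry no label.

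The objective served is secondary (Section 4): "To compare the site (Technician) burden between three new EEG systems and a standard clinical EEG system". Its endpoints there are set-up and clean-up timings, the interim debriefs on ease of clean-up, the daily exit debrief and the end-of-study one, described as "Exit debrief at the end of the study including a subjective rank ordering of devices for the best and the worse one", with reasons for the choice. The 1–4 grid is not named.

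On analysis, Section 10.5.1 plans "For all quantitative questionnaires (VAS) as well as the timing data, univariate statistics and linear modelling" for device differences. For the remaining answers it says "Summary overviews of overall preferred rank orders and answers to specific questions will be constructed". Section 11.2 adds, in general terms, that similar methods will be applied to questionnaire data to give an overall description.

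**The concern.** A comparative scale should let the rater depart from neutral equally far in both directions. Here there is one step below *identical* and two above it. No form offers *much worse*, so a device that is far slower to set up receives the same code as one that is slightly slower, while the mirror-image advantage gets two separate codes.

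The end-of-study form adds a second defect. It gives four codes with only the ends named, so a technician who sees no difference has no stated place to answer. The top anchor also changes from *much* better, a statement of size, to *definitely* better, a statement of certainty.

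This grid is the only staff item that asks for a direct rating of each new device against the reference, topic by topic. The Appendix 3 VAS items rate one device at a time, and the ranking is a single overall preference. The study exists to compare the new devices with a reference, and its rationale already expects less burden from them, so the item should be able to register both directions. A degree of *worse* that was never offered cannot be recovered in the analysis.

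**Working it through.** The protocol gives no figure for this item, so there is nothing of its own to reproduce. The check counts the options and then works out what the coding does.

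**1. Count of options (training and dummy-run forms).** Unfavourable 1 of 4 (25%), neutral 1 of 4 (25%), favourable 2 of 4 (50%). The neutral code is 2; the midpoint of the codes is (1+4)/2 = 2.5.

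**2. Effect of averaging the codes.** Suppose opinion would fall on a balanced scale in shares *a* (much worse), *b* (worse), *c* (identical), *d* (better), *e* (much better). The form merges *a* and *b* into code 1, so

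mean = 1(*a*+*b*) + 2*c* + 3*d* + 4*e*.

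The deviation from neutral is −(*a*+*b*) + *d* + 2*e*. The balanced scale gives −2*a* − *b* + *d* + 2*e*. The form therefore exceeds the balanced scale by exactly *a*, the share who would have said *much worse*. The direction is fixed; the size depends on *a*, which the protocol does not give.

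Two assumed spreads with no net difference:

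- 10/20/40/20/10%: 0.1×1 + 0.2×1 + 0.4×2 + 0.2×3 + 0.1×4 = 2.10, against neutral 2.00.
- 20% in each: 0.2×(1+1+2+3+4) = 2.20, against neutral 2.00.

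**3. Range under a second assumption.** Take the perceived difference as normal, with cut-points at ±0.5 and ±1.5. The cut-points, the means and the SDs are all assumptions.

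| Mean | SD | Form, deviation from neutral | Balanced scale |
|---|---|---|---|
| 0 | 0.5 | +0.001 | 0 |
| 0 | 1 | +0.067 | 0 |
| 0 | 2 | +0.227 | 0 |
| +1 | 1 | +0.93 | +0.93 |
| −1 | 1 | −0.62 | −0.93 |
| +2 | 1 | +1.62 | +1.62 |
| −2 | 1 | −0.93 | −1.62 |

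With no true difference the tilt is small unless opinions vary widely. The larger effect is compression: a strongly worse device scores −0.93 where its mirror image scores +1.62.

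**4. Effect on counts.** Using the same two spreads, worse / identical / better-or-much-better is 30/40/30% and 40/20/40%. Both are symmetric. On the two fully labelled forms a count by direction is unbiased, and only the degree of *worse* is lost.

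**5. End-of-study form.** The count in step 4 needs to know which code means *identical*. The earlier forms put it at 2. A rater who sees only the end labels may take the centre, which lies between 2 and 3. The form does not settle this, so even a count by direction rests on an assumption there.

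**The case against.** The strongest case against is that little depends on this grid. That largely stands.

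- It is not a named endpoint. Timings, the clean-up debrief and the rank orders carry the site-burden objective.
- A badly performing device would show elsewhere. Set-up and clean-up times are measured. In Appendix 3, the VAS item "How easy was it to set-up the device" and its clean-up counterpart run between opposite anchors of equal strength. Participants rate comfort themselves, and staff rank all four systems and explain the worst choice. The end-of-study form says its questions define the preference list, but it also asks for an explicit ranking, so preference does not depend on the grid.
- Linear modelling is stated for VAS and timing data. For other answers, summaries are planned, and no mean of the grid is specified.

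Some stronger readings are tempting, and the document does not support them. A reader might infer that the site-burden results as a whole favour the new devices; the endpoints just listed do not use this scale. A reader might infer that category summaries are biased by construction; step 4 shows that they are not on the two fully labelled forms. A reader might say that change from expectation to end of study cannot be interpreted; the wording does differ between forms, but the protocol plans no such change analysis. A reader might also take 2.5 as the average of uninformative answers, half a point above neutral; that requires trained staff to answer evenly over the four options, which nothing in the protocol suggests.

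What remains is that the options are fixed in the protocol, the answers may be summarised and, given the broad wording of Section 11.2, averaged, and the missing category cannot be restored afterwards.

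**Conclusion.** The point holds as a minor defect of one ancillary instrument. The training and dummy-run forms are unbalanced, with one unfavourable option against two favourable ones, and the end-of-study form leaves *identical* without a stated position. Two things follow from the form alone: degrees of *worse* cannot be recorded, and any average of the codes is too high by the share of raters who would have chosen *much worse*.

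That share cannot be found from the protocol. The figures of 2.10 and 2.20 against 2.00, and +0.001 to +0.227 under the normal model, illustrate assumed distributions and are not estimates for this study. The tilt is close to nil if most answers sit near *identical*. Nothing here touches the primary signal-quality objective or the timings, VAS items and rank orders.

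**What to change.** Use one balanced five-point scale on the training, dummy-run and end-of-study forms: much worse, worse, identical, better, much better. Label every point and use the same words on all three forms. If numeric codes are wanted, run them from −2 to +2 with *identical* at 0.

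The cost is an edit to three questionnaire tables before use. It adds no visit, participant burden or sample size. If forms have already been completed, report the grid as counts rather than means, and for the end-of-study form state which code was taken as neutral and that the form did not define it.
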